### Sample size

In order to reliably measure the quantitative primary outcomes following completion of the GST treatment and continued CBT-E treatment, a two-tailed alpha of 5%, a power of 90% and a medium effect size of d = 0.50 is assumed. This yields a sample size of 86 patients per treatment arm, thus *N* = 172 in total for a classical RCT. However, there is clustering in the GST arm due to its group format for treatment delivery. Therefore, an additional design effect is needed to correct the GST sample size for potential clustering. Assuming a group size of 8 participants and an intra-class correlation of 0.10, a design effect of 1.70 was computed. When multiplying this design effect with the original sample size of the GST arm (*N* = 86), the adjusted necessary sample size for the GST arm is equal to 1.70 *86 = 146 participants. Adding the initial number of participants in the continued CBT-E arm (*N* = 86), the total number of necessary study participants is equal to *N* = 232.

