#### Process evaluation

In order to measure the extent to which GST is a feasible alternative to CBT-E in clinical practice for patients and therapists, process evaluations will be conducted. More specifically, treatment fidelity (treatment quality), dose delivered (completeness), dose received (exposure and satisfaction), and reach (participation rate) will be assessed in both the GST arm and the continued CBT-E arm.

I.In order to assess dose received, i.e. treatment satisfaction and overall therapeutic alliance, patients will complete a session rating scale (SRS) during each treatment session. The SRS consists of 4 questions regarding key dimensions of effective therapeutic relationships [53].

II. To assess dose delivered and reach, therapists will complete patient registration files after each session. In these files, therapists can describe patient attendance and the extent to which treatment was delivered according to protocol, including potential deviations and additional therapies or medications. These files are expected to assess the true implementation characteristics of the treatment protocol in Dutch clinical practice.

III. Recording of therapy sessions will take place regularly in order to rate overall compliance to the treatment protocol, quality of treatment delivery and the number of patients that were able to participate (fidelity, dose delivered and reach).

IV.After the end of treatment, qualitative interviews will be conducted among certain patients from the GST arm and the continued CBT-E arm, which will take approximately 30 min. Using existing guidelines for qualitative data collection and analysis [54], these interviews are aimed at generating original findings regarding patient experiences that are not identifiable through quantitative approaches. Building upon the SRS, these interviews may identify profound data regarding treatment satisfaction and therapeutic alliance.

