In order to verify the robustness of the obtained ICER and ICUR, non-parametric bootstrapping techniques will be conducted. These bootstrap replications are characterized by random sampling based on individual input data, yielding information about the magnitude and distribution of most pairwise cost-effect estimates. In order to facilitate this objective, the bootstrap replications will yield the 95% confidence intervals for the obtained ICER and ICUR within a cost-effectiveness plane, surrounding the 2.5th and 97,5th percentiles [29]. While the horizontal axis of a cost-effectiveness plane depicts the difference in effectiveness between two treatments, the vertical axis represents the cost difference between two treatments [59].

Subsequently, a cost-effectiveness acceptability curve will be plotted in order to determine the maximum amount of money that society is willing to pay for one unit of clinical improvement or one unit of QALY gains. This maximum amount of money is also called the willingness-to-pay (WTP) ceiling ratio [29]. In the Dutch healthcare system, ceiling ratios of € 20,000, € 50,000 and € 80,000 per QALY exist, depending the disease burden that will be determined based on the study population [60]. If the computed ICER or ICUR for a certain treatment is likely to fall below these thresholds, that treatment is usually considered cost-effective. In order to determine whether GST is cost-effective over CBT-E in the Netherlands, the cost-effectiveness acceptability curve will display the probability that the ICER and ICUR of GST fall below a range of existing ceiling ratios. This computed probability is based on the obtained bootstrap replications for the ICERs and ICURs of GST. Lastly, multivariate sensitivity analyses will be conducted to examine whether different assumptions regarding cost prices and volumes may affect the obtained ICERs and ICURs.

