#### Process evaluation

Data on process evaluation will be analyzed, using qualitative and quantitative methods. Data from the qualitative interviews will be used to explore and distill relevant themes regarding treatment experiences among patients during the trial.

In principle, we aim to record 10% of administered sessions with audio devices in order to assess whether treatment sessions have been implemented according to protocol. Furthermore, quantitative data from items on the session rating scales (SRS) will be analyzed, using descriptive statistics in SPSS. For example, descriptive statistics per SRS item in both treatment arms may include: medians, means and frequencies. Using t-test analysis, differences in SRS outcomes between both treatment arms will be examined quantitatively in order to determine whether GST is more feasible than CBT-E for patients.

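### The GST arm is enlarged for group clustering, but as written the economic bootstrap and the SRS t-test treat its patients as independent, so their error bars are moderately too narrow

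*Protocol article*

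**What the plan says.** All references are to the protocol article.

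- **Sample size.** The section states that "there is clustering in the GST arm due to its group format for treatment delivery". It continues: "Assuming a group size of 8 participants and an intra-class correlation of 0.10, a design effect of 1.70 was computed". It concludes that "the adjusted necessary sample size for the GST arm is equal to 1.70 *86 = 146 participants". The CBT-E arm stays at 86, for a total of 232. The Randomization section gives the same cluster effect as the reason for allocating CBT-E to GST in a 1:2 ratio.
- **Data analysis, Clinical effectiveness.** The multilevel models are to allow for correlation between time points and for nesting.
- **Data analysis, Economic evaluation.** Uncertainty comes from a non-parametric bootstrap: "These bootstrap replications are characterized by random sampling based on individual input data". The same replications supply the 95% intervals for the ICER and ICUR and the probabilities on the acceptability curve. The only sensitivity analyses named for the ICER and ICUR vary cost prices and volumes.
- **Process evaluation.** Under Data collection, "patients will complete a session rating scale (SRS) during each treatment session". Under Data analysis, "Using t-test analysis, differences in SRS outcomes between both treatment arms will be examined quantitatively", in order to judge whether GST is the more feasible treatment for patients.

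The economic and process analysis sections mention neither therapy groups nor a multilevel method.

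**The concern.** Drawing patients one at a time, or applying an ordinary two-sample t-test, treats members of one GST group as independent. The sample size section says that they are not. If outcomes within a group are positively correlated, the true variance of the GST mean exceeds what either method estimates, and for any positive correlation the results look more precise than they are.

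The mismatch is clearest for the EDE-Q. It is the primary outcome, the intra-class correlation of 0.10 was assumed when sizing for the primary outcomes, and EDE-Q gains are the article's example of the effect in the ICER. The same EDE-Q difference could therefore carry a cluster-adjusted standard error in the clinical results and an unadjusted one on the cost-effectiveness plane.

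At stake are the spread on that plane, the acceptability curve that decision makers will read, and the SRS comparison. Cost-effectiveness is one of the trial's three stated research areas, and the named sensitivity analyses would not reveal the problem.

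**Working it through.** **Inputs from the article.** The Sample size section gives "a two-tailed alpha of 5%, a power of 90% and a medium effect size of d = 0.50 is assumed", 86 per arm before correction, groups of m = 8, intra-class correlation (ICC) 0.10, and arms of 86 (CBT-E) and 146 (GST). CBT-E is delivered in individual sessions, so only the GST arm has therapy-group clustering.

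**Step 1: reproduce the plan's figures.** The two-sample t-test solution for d = 0.50, two-sided 5% and 90% power is 85.03 per arm, rounded up to 86. Design effect: 1 + (8 − 1) × 0.10 = 1.70. GST arm: 1.70 × 86 = 146.2, stated as 146. Total: 146 + 86 = 232. All agree.

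**Step 2: standard error of an arm difference (outcome SD = 1 in both arms).**

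- Individual level: √(1/146 + 1/86) = √0.018477 = 0.1359.
- With GST clustering: √(1.70/146 + 1/86) = √0.023272 = 0.1526.
- Variance ratio: 0.023272 / 0.018477 = 1.26. The correct standard error is √1.26 = 1.12 times the individual-level one. Inverted, 0.1359 / 0.1526 = 0.891, so the individual-level value is about 11% too small.

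**Step 3: consequences.** Real coverage of a nominal 95% interval is 2Φ(1.96 × 0.891) − 1 = 91.9%. Real error of a 5% t-test is 1 − 0.919 = 8.1%. For the acceptability curve, net benefit at a fixed ceiling ratio is also a difference in means, so if the same ICC applied, a reported probability of 95% (z = 1.645) should read Φ(1.645 × 0.891) = about 93%.

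**Step 4: range of ICC.** The article gives no ICC for costs, QALYs or the SRS, so the values other than 0.10 are assumptions.

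| ICC | Design effect | Individual-level SE / correct SE | Real coverage of 95% interval | Real error of 5% test |
|---|---|---|---|---|
| 0.01 | 1.07 | 0.987 | 94.7% | 5.3% |
| 0.05 | 1.35 | 0.941 | 93.5% | 6.5% |
| 0.10 (plan) | 1.70 | 0.891 | 91.9% | 8.1% |
| 0.20 | 2.40 | 0.811 | 88.8% | 11.2% |

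A literal 1:2 split of 232 (77 and 155) at ICC 0.10 gives a ratio of 0.90 and coverage of about 92%, so the conclusion does not depend on which split is realised.

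**Step 5: simulation.** This used 4,000 trials with 86 CBT-E patients and 146 GST patients (18 groups of 8 and one of 2), ICC 0.10, no true difference and 400 bootstrap draws each. The t-test rejected in 8.0%. The percentile interval from resampling individuals covered 91.0%; resampling whole GST groups raised this to 94.0%.

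**The case against.** **The phrase about individual data may only describe bootstrapping in general.** It could mean patient-level cost-effect pairs as opposed to aggregate data. The section calls itself a general plan, and a full analysis plan may specify group-wise resampling. This is a fair caution, and it is why the point is limited to what is written. It does not remove the point: the article names a resampling unit and a test, and neither fits the structure that it assumes elsewhere.

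**The ICC was assumed for the primary outcomes only.** This stands. For costs, QALYs and the SRS the size of the error is unknown and could be negligible: at 0.01 the interval is almost right. The plan's own value carries over directly only to the EDE-Q axis.

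**The article describes no 5% test of the ICER.** Also correct. For the economic analysis the relevant measures are interval coverage and the acceptability probabilities; the 8% error belongs to the SRS t-test.

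**Stronger readings that the article does not support.**

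- A reader might infer that the SRS test has a very high false-positive rate, because ratings are taken at every session. If session records were analysed as independent rows, with 26 GST sessions, 22 CBT-E sessions (the midpoint of 12 to 32) and an assumed within-patient correlation of 0.3 to 0.7, the standard error would be 2.8 to 4.1 times too small and the error 48% to 63%. But the article does not state the unit of analysis. One mean per patient fits its wording equally well; it removes the repeated-ratings problem and leaves only the group effect.
- A reader might take the 1.70 as inflating the whole sample. It applies to the GST arm; the total rises from 172 to 232, a factor of 232/172 = 1.35.
- A reader might extend the problem to the primary result. The clinical models provide for nesting, so that does not follow.

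**Conclusion.** The concern holds in a limited form. As written, the bootstrap and the SRS t-test do not reflect the GST clustering on which the sample size and allocation ratio rest. At the plan's ICC of 0.10, with groups of 8 and arms of 86 and 146, the individual-level standard error is about 11% too small, coverage is about 92% instead of 95%, and a 5% t-test has about 8% error. The effect is moderate because only one arm is clustered.

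The direction is the same for any positive ICC. The size rests on equal outcome variances in the two arms, groups of 8, and, for costs, QALYs and the SRS, an ICC that the article does not give (coverage 94.7% to 88.8% over 0.01 to 0.20). Repeated SRS ratings would add much more error only if session records were the unit, which is left open. The affected results are the economic evaluation and the SRS comparison. The change should be made before the data are analysed.

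**What to change.** 1. **Define the GST cluster in advance and record its identifier for each patient.** Groups are half-open with entry and exit every 13 weeks, so membership overlaps and the cluster has to be chosen, for example the continuing group or the entry cohort within it. The article does not say that a group identifier is kept; the therapists' per-session registration files are a natural place for it.
2. **Bootstrap.** Resample GST groups (whole, or groups and then patients within them) and individual CBT-E patients, stratified by arm, keeping each patient's cost and effect together. Do not also stratify by location: 146/8 is about 18 groups, and the recruitment section lists 11 locations, so there would be fewer than two groups per location on average. A location with one group would return that group in every draw.
3. **SRS.** State the unit of analysis and replace the t-test with a mixed model that has a patient random effect and, in the GST arm, a group random effect. Use post-randomisation sessions only, since ratings are also collected during phase 1 CBT-E.

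The cost is modest: changed analysis code, one extra identifier and somewhat wider intervals (about 12% at ICC 0.10). With so few groups, group resampling is not perfect either: it reached 94.0% in the simulation.

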#### Economic evaluation

**Base-case analysis.** Using a micro-costing and bottom-up approach, total costs will be approximated from a societal perspective in the GST arm and the continued CBT-E arm, in line with recent best practices [52]. Essentially, each element of service use will be multiplied by an appropriate unit cost in euros. If necessary, unit costs will be updated, using the 2023 consumer price index [55]. Relevant unit costs for each type of service are outlined in contemporary Dutch costing manuals for healthcare services [56, 57]. Intervention costs, healthcare costs, patient and family costs and productivity losses for unpaid work, paid work and education will be estimated. Productivity losses will be quantified, using a friction cost approach that is confined to the time period required to replace one sick employee. In case of major uncertainty surrounding the abovementioned analyses, cost estimates will be founded on the most conservative assumptions.

Primarily, economic evaluations aim to compare the additional costs and outcomes of GST to those of CBT-E. In the economic evaluation of the current protocol, collected data will be used to conduct a cost-effectiveness analysis (CEA) and a cost-utility analysis (CUA). On the one hand, a CEA expresses all clinical treatment effects of GST and CBT-E relative to their economic costs, using the incremental cost-effectiveness ratio (ICER). On the other hand, a CUA aims to compare all gains in quality adjusted life years (QALYs) of GST and CBT-E to their respective economic costs, using the incremental cost-utility ratio (ICUR).

In short, the ICER is aimed at dividing the difference in treatment effects of GST and CBT-E by the difference in total costs of both treatments. For instance, the total difference in clinical EDE-Q gains of both GST and CBT-E can be weighed against the cost differences of both treatments. Using a similar incremental cost-utility ratio (ICUR), the difference in QALY gains of both treatments is divided by their respective cost differences. QALYs are computed based on the measured EQ-5D-5 L data, using converted EuroQol utility scores [58].

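### The acceptability curve counts bootstrap ratios that fall below a ceiling, a rule that misclassifies every replicate in which GST is less effective; the ratio's percentile limits and the use of per-QALY ceilings for the ICER are separate, smaller faults.

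*Protocol article*

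**What the plan says.** All of this is in the protocol article, Data analysis, Economic evaluation.

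- **Ratios.** The ICER is built on clinical effects; the example is that "the total difference in clinical EDE-Q gains of both GST and CBT-E can be weighed against the cost differences of both treatments". The ICUR is built on QALYs from the EQ-5D-5L.
- **Intervals.** The bootstrap is to give "95% confidence intervals for the obtained ICER and ICUR within a cost-effectiveness plane, surrounding the 2.5th and 97,5th percentiles".
- **Ceilings.** The text says that "ceiling ratios of € 20,000, € 50,000 and € 80,000 per QALY exist", depending on disease burden. It continues: "If the computed ICER or ICUR for a certain treatment is likely to fall below these thresholds, that treatment is usually considered cost-effective".
- **Curve.** The rule is that "the cost-effectiveness acceptability curve will display the probability that the ICER and ICUR of GST fall below a range of existing ceiling ratios". On the source of that probability: "This computed probability is based on the obtained bootstrap replications for the ICERs and ICURs of GST".

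The section gives no net-benefit rule and no rule by quadrant of the cost-effectiveness plane.

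**The concern.** A ratio below the ceiling marks cost-effectiveness only when GST is the more effective arm. When GST is less effective, dividing by a negative number reverses the inequality, so a count of ratios below the ceiling gives the wrong answer for each such replicate. The probability that GST is cost-effective would then be wrong on the curve itself. Cost-effectiveness is one of the trial's hypotheses (Objectives, Economic evaluation), and the results are meant for policymakers and insurers (Implications for healthcare policy and clinical practice). The rule fails most when the QALY difference is small or uncertain, which is when readers lean on the curve.

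Two further points sit beside this one and do not cause the miscount. Percentiles of a ratio lose their meaning when its denominator takes both signs. And a ceiling in euros per QALY says nothing about euros per EDE-Q point.

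**Working it through.** The plan states no acceptability probability and no ICER limit, so there is no figure of its own to reproduce. The rule is tested first by sign, then by size.

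**1. By sign (illustrative points only).** Let dE be the QALY difference, dC the cost difference (GST minus CBT-E) and L the ceiling. The ratio is dC/dE and the net benefit is L x dE - dC. GST is cost-effective when net benefit exceeds 0.

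| GST is | dE | dC | Ratio | Net benefit at 20,000 / 50,000 / 80,000 | Ratio rule |
|---|---|---|---|---|---|
| dearer, worse | -0.05 | +3,000 | -60,000 | -4,000 / -5,500 / -7,000 | passes, wrongly |
| cheaper, better | +0.05 | -3,000 | -60,000 | +4,000 / +5,500 / +7,000 | passes, rightly |
| cheaper, worse | -0.05 | -500 | +10,000 | -500 / -2,000 / -3,500 | passes, wrongly |
| dearer, better | +0.05 | +500 | +10,000 | +500 / +2,000 / +3,500 | passes, rightly |

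The ratio cannot separate dominated from dominant. In general, dC/dE < L is the same as net benefit > 0 when dE > 0, and the same as net benefit < 0 when dE < 0. So the ratio rule gives

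P(net benefit > 0) + P(dE < 0 and net benefit < 0) - P(dE < 0 and net benefit > 0).

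The error can have either sign, and it disappears when P(dE < 0) is near zero.

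**2. By size (assumed replicates).** Replicates are taken as normal and independent, with SD EUR 1,500 for the cost difference and 0.03 for the QALY difference. These SDs are assumptions. The correct value is Phi[(L x dE - dC) / sqrt((L x 0.03)^2 + 1,500^2)]. At L = 20,000 the denominator is sqrt(600^2 + 1,500^2) = 1,615.5. For the dominated case this is Phi[(-400 - 3,000)/1,615.5] = Phi(-2.10) = 0.018. The ratio rule was counted by simulation. At no difference it can be checked directly: 0.5 + arctan(600/1,500)/pi = 0.62.

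| Mean dC, dE | Ratio rule at 20,000 | Net benefit at 20,000 |
|---|---|---|
| +3,000, -0.02 | 75% | 2% |
| +1,500, 0 | 58% | 18% |
| 0, 0 | 62% | 50% |
| +1,000, +0.03 | 50% | 40% |
| -1,000, +0.03 | 78% | 84% |
| +1,000, +0.08 | 65% | 64% |

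**3. Other assumptions.** Patient-level SDs of 0.25 QALY and EUR 15,000, with the planned 146 and 86 patients (Sample size), give standard errors of 0.25 x sqrt(1/146 + 1/86) = 0.034 and 15,000 x sqrt(1/146 + 1/86) = 2,039. With dE = -0.03 and dC = +2,000 the ratio rule gives 0.78 / 0.83 / 0.87 at the three ceilings, against 0.11 / 0.09 / 0.10. Varying the QALY SD (0.20 to 0.30), the cost SD (8,000 to 25,000), the correlation (-0.3 to 0.3) and the GST design effect (1.0 or 1.7) moves these to 0.69-0.90 against 0.02-0.23. With dE = +0.03 and dC = +1,000 the values are 0.52 / 0.69 / 0.79 against 0.43 / 0.58 / 0.66.

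**4. Percentile limits.** In that last case about 19% of replicates have dE < 0 (0.130 + 0.058). The point ratio is 1,000/0.03 = 33,333, but its percentiles run from about -547,000 to +607,000 and mix all four quadrants. For EDE-Q at the planned d = 0.50 with an effective 86 per arm, the standard error is sqrt(2/86) = 0.152. Then 0.50/0.152 = 3.28, and only about 0.05% of replicates would be negative.

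**The case against.** The best defence is that the section explains a concept and does not specify a count. It keeps cost-effect pairs and puts them on a plane with effect across and cost upwards. There a ceiling is a line through the origin, and points under the line are exactly those with positive net benefit, so a dearer-and-worse point lies above it. Falling below a ceiling is also common shorthand, and the full plan may use net benefit. That reading is possible, and nothing shows which rule will be coded. But the article says that the probability comes from replications of the ratios, and it gives no other rule.

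Other parts of the defence stand:

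- The figures take the ratio as cost over effect. The article writes both ratios as effect over cost, which is a separate error. The percentages therefore describe the counting rule applied to a conventional ratio, not the text followed word for word throughout.
- A reader might infer that GST's probability is always overstated. It is not: the cheaper-and-better case at EUR 20,000 is understated.
- A reader might infer that the percentile limits produce the miscount. They do not; they are a second fault of the same ratio, and it matters only when the effect difference crosses zero.
- A reader might infer that EDE-Q results will be judged only against QALY ceilings. The section does mention willingness to pay per unit of clinical improvement, so a curve in that unit seems intended. What remains is that no ceiling or range is given in that unit, and that the sentence on the thresholds names both ratios.

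**Conclusion.** The concern holds in this form. Followed as written, with the ratio read as cost per effect, the rule counts dearer-and-worse replicates as cost-effective and reverses cheaper-and-worse ones. That follows from signs alone and needs no assumed figure.

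The size does need assumptions, because the documents give no cost or QALY SDs or expected differences. Under those used here the error runs from negligible, when nearly all replicates show a QALY gain, through about 10 points when GST is dearer and modestly better, to over 70 points when GST is dominated. It is usually in GST's favour in these scenarios, but not always.

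The percentile limits are a real problem for the ICUR if the QALY difference is small, and much less so for an EDE-Q ratio at the planned effect. The ceiling point is loose wording that needs tying down. The documents do not show that the analysts will in fact count this way; they show that the published rule tells them to.

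**What to change.** - Define the curve as the share of paired bootstrap replicates with ceiling x effect difference - cost difference above zero, plotted over the range of ceilings.
- Report confidence intervals on net benefit at each ceiling. Give the ICER and ICUR as point estimates, with the plane and the share of replicates in each quadrant, in place of percentile limits of the ratio.
- Use the EUR 20,000, 50,000 and 80,000 ceilings for the ICUR only. For EDE-Q, show the curve over a separate stated range of euros per point.

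The cost is a few sentences and about one line of code on the same bootstrap output. No data collection, sample size or primary analysis changes.
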